### 1.3. Main hypotheses

The following are the principal hypotheses of the study, and the numbering of the hypotheses is linked to the numbering of the objectives (e.g., H1.1 designates the hypothesis linked to the objective O1.1, Hbase designates the hypothesis at baseline, i.e., before randomization and the experimental procedure).

(H1.1) (a) Measures pertaining to S-ART will be significantly higher in SPs who receive MT compared to those who receive RT and thus, at post-training and at follow-up. The only measure that we hypothesize to be equally lower for both groups (at both time points) is stress. (b) Within-groups effects (i.e., among the three time points) will be significant for all the outcomes for the MT group, and only for stress for RT.

(H1.2) (a) The effects of MT on S-ART measures will be moderated by the adherence of the SPs to the practice at both time points (i.e., post-training and follow-up). (b) The effects of RT on stress will be moderated by the SPs’ adherence to practice.

(H2.1) (a) Objective and subjective measures pertaining to the quality of the SP-SR interactions will be significantly higher in dyads with a SP who received MT compared to dyads with a SP who received RT at both time points (i.e., post-training and follow-up). (b) Within-groups effects (across time) will be only significant for the dyads with an SP who received MT.

(H2.2) The effects of MT of the SPs on the quality of SP-SR interactions (measured subjectively and objectively) will be mediated by the increase on S-ART of the SPs at both times points (i.e., post-training and follow-up).

(H3.1) SRs who interacted with SPs who received MT training will show significantly (a) higher positive emotional states, lower negative emotional states and (b) higher mindfulness states following their interaction compared to those who interacted with SPs who received RT and thus, at both time points (i.e., post-training and follow-up). (c) Within-groups effects will be only significant for the SR who interacted with an SP with MT training.

(H3.2) The effects of MT of the SP on the emotional and mindfulness states of the SR will be mediated by the increase in the quality of the SP-SR interaction and moderated by SRs’ Fears of Compassion from Others (i.e., higher fears of compassion will reduce the mediation effects) at both time points (i.e., post-training and follow-up).

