## 2. Methods and design

### 2.1. Participants

We aim to recruit 640 adult community members (18–35 years old, 50% female) through advertising on social media. The sample size was based on detecting significant differences among the groups (i.e., between SPs with MT vs. SPs with RT), assuming a moderate effect (Khoury et al., 2013a,^2015^), a power of 0.8 and an alpha of 0.05 (Cohen, 1977) and the expectation 15 to 20% attrition rate. We will exclude participants who: (1) have a regular meditation practice; (2) have already participated in a formal mindfulness training (such as MBSR or a meditation retreat); or (3) had a social support skills training (e.g., counselors, psychologists, social workers, or other medical personnel).

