#### 2.5.2. Experiment–Part II; mindfulness/relaxation training

SPs (total of 160) will be asked to complete measures of mindfulness, perceived stress, emotion regulation, empathy, compassion for others, active listening, perspective taking and interpersonal mindfulness. Then, they will be randomly and equally divided into two groups using a computer algorithm to ensure randomization and concealment. Half of the SPs (80) will receive the MT (MBSR-ld) and the other half will receive the RT. Participants in both groups will be asked to complete the daily logs during the 8 weeks. After the training, the same measures will be administered to the SPs.

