## 3. Data analyses strategies

To ensure data reliability, self-reported data will be inspected for normality and skewness and outliers will be eliminated. Interrater reliability for the behavior observation data will be computed. An interrater coefficient of 0.95 or above is expected.

To test H1.1, H2.1, and H3.1, we will perform a mixed (2 groups × 3 time-points) multivariate analysis of covariance (MANCOVA) controlling for social desirability (and for Fears of Compassion from Others for H3.1). MANOVA/MANCOVA allow to reduce Type-I errors (i.e., rejecting the null-hypothesis when it is true, correcting therefore for multiple comparisons) when testing changes in multiple dependent variables. To test H1.2, we will use a regression analysis. To test H2.2 and H3.2, we will use a path analysis. To test associations and meditation/moderation at baseline (Hbase), we will use correlations and PROCESS macro with 5,000 bootstrapped/bias-corrected confidence intervals (Hayes, 2018). Structural Equation Modeling (Klem, 2000) may be used as well if the power is sufficient.

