Regarding the dyadic data, we will use the Actor-Partner-Interdependence-Model (APIM; Kenny and Judd, 1986; Kenny and Malloy, 1988; Griffin and Gonzalez, 1995; Kenny, 1996; Kenny et al., 2020) and APIM-M (M for mediation) as we cannot assume independence between the members of the dyad (Gonzalez and Griffin, 2012). APIM/M allows us to test the interactions between the SP and the SR scores on a given predictor (Kenny et al., 2020). To calculate power for the APIM/M, we used a Monte Carlo simulation (Schoemann et al., 2014), which is applicable for APIM/M (Ledermann et al., 2022). Results suggested that 80 dyads per group should be sufficient (powered enough) to detect moderate effects (i.e., changes between baseline, post, and follow-up time points) for an alpha of 0.05. In addition, if for some dependent variables, the power is insufficient to detect a change, we will use Bayesian Analysis (Fitzpatrick et al., 2016) instead of APIM/M as authors have previously recommended (Sagan and Kowalska-Musiał, 2009; Ledermann et al., 2022). All the statistical analyses will be conducted using R (R Core Team, 2021). If multiple statistical analyses (e.g., *post hoc* ANOVAs or *t*-tests) are to be conducted sequentially on the same set of dependent variables, the level of significance (alpha) will be divided by the number of tests (multiple comparisons correction) to reduce the risk of false positives (i.e., reducing Type-I errors).

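### Follow-up tests are corrected by plain Bonferroni; Holm's procedure on the same family gives the same error control, never rejects less, and costs one sentence

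*Protocol article*

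**What the plan says.** Section 3 (Data analyses strategies) of the protocol article names the main test for H1.1, H2.1 and H3.1: "we will perform a mixed (2 groups × 3 time-points) multivariate analysis of covariance (MANCOVA"), adjusted for social desirability and, for H3.1, for fears of compassion. The same section adds a conditional rule. If several analyses, with post hoc ANOVAs or t-tests as examples, "are to be conducted sequentially on the same set of dependent variables", then "the level of significance (alpha) will be divided by the number of tests (multiple comparisons correction"). No step-down method is mentioned, and the number of follow-up tests is not given.

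Section 1.3 words the hypotheses at the level of measures. For H1.1, "Measures pertaining to S-ART will be significantly higher in SPs who receive MT compared to those who receive RT", at post-training and at follow-up, with stress the one measure expected not to separate the groups. H3.1 names positive affect, negative affect and state mindfulness, again at both time points.

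Section 2.1 bases the sample size on "a power of 0.8 and an alpha of 0.05", "assuming a moderate effect" and "the expectation 15 to 20% attrition rate". Section 2.5.2 gives the arm size: "Half of the SPs (80) will receive the MT (MBSR-ld) and the other half will receive the RT".

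**The concern.** A MANCOVA can show that the groups differ somewhere in a set of outcomes. It cannot show which measures differ. Because H1.1 and H3.1 make claims about individual measures, follow-up tests are very likely to be run, and the correction rule then decides which of those claims succeed.

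Bonferroni tests every p-value at alpha/m. Holm tests the smallest at alpha/m, the next at alpha/(m−1), and so on, stopping at the first failure. Both keep the family-wise error at or below alpha whatever the correlation between tests, and Holm's later thresholds are never stricter. Where several effects are real, Bonferroni therefore misses some that Holm would find, with nothing gained in error protection. The plan predicts this situation: a true MT-over-RT difference on nearly every outcome.

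**Working it through.** **Inputs from the article.** Alpha 0.05, power 0.8, a moderate effect with no number, attrition 15 to 20% (section 2.1); 80 SPs per arm (section 2.5.2).

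**Assumptions.** d = 0.5 with SD 1; two-sided tests; equal correlation rho between test statistics; independent SPs; no gain from covariates or repeated measures. The article gives none of these, nor the number of tests m or the share of real effects, so ranges are shown.

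**1. The plan's own figure.** A two-sample t-test at d = 0.5, alpha 0.05 and power 0.8 needs 64 per arm. With 20% attrition, 64 / (1 − 0.2) = 80, the stated arm size. At 15%, 64 / 0.85 rounds up to 76. So d = 0.5 with 64 evaluable per arm is a fair reading of the plan.

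**2. Power at a divided alpha.** The noncentrality is 0.5 × √(64/2) = 2.83. Power is about Φ(2.83 − z), where z is the two-sided critical value at 0.05/m.

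| m | z | Power per effect, Bonferroni |
|---|---|---|
| 1 | 1.96 | 81% |
| 2 | 2.24 | 72% |
| 3 | 2.39 | 67% |
| 4 | 2.50 | 63% |
| 6 | 2.64 | 58% |
| 8 | 2.73 | 54% |

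The stated power of 0.8 applies to the first row only.

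**3. Holm against Bonferroni.** For each setting, 200,000 sets of m equicorrelated z-tests were simulated with 64 per arm, d = 0.5 and rho from 0 to 0.5. Entries are average power per real effect.

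| Family | Bonferroni | Holm | Gain (points) |
|---|---|---|---|
| 2 tests, both real | 72% | 77–78% | 5 to 6 |
| 3 tests, all real | 67% | 75–76% | 8 to 9 |
| 4 tests, all real | 63% | 72–74% | 9 to 11 |
| 6 tests, all real | 58% | 68–70% | 10 to 12 |
| 8 tests, all real | 54% | 65–66% | 11 to 12 |
| 8 tests, 7 real | 54% | 62–63% | 8 to 9 |
| 3 tests, 2 real | 67% | 70% | 3 to 4 |
| 4 to 16 tests, half real | – | – | 2 to 3 |
| Any family, 1 real | – | – | 0 to 0.2 |

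The row with 7 of 8 real corresponds to the eight SP outcomes of Table 1 with stress null. The row with 3 of 3 real corresponds to the three SR outcomes of H3.1 at one visit. At rho = 0.8 these two gains fall to 7.4 and 6.4 points. With 80 per arm and no attrition, the half-real gain reaches 3.9 points and the largest gain is about 14.

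The chance of finding at least one effect rises by at most 0.2 points, because the smallest p-value still faces alpha/m. Holm rejected everything Bonferroni rejected in every set, and its family-wise error stayed at or below 0.05.

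**4. Smaller effects (rho = 0.4, 64 per arm).** With six of six real, power goes from 17% to 21% at d = 0.3 and from 6.6% to 7.6% at d = 0.2. With seven of eight real at d = 0.3, it goes from 15% to 17%.

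**5. Requiring a multivariate test first.** Hotelling's T-squared on the group difference stood in for the MANCOVA. With t-tests, the eight-outcome case at one visit went from 51–52% to 59–60%, and the three SR outcomes at two visits from 56% to 67–68%. The gain is essentially unchanged.

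**6. Definition of the family.** In t-test simulations of the eight SP outcomes with stress null, Bonferroni at one visit gave 52%, and Holm pooled over both visits (16 tests) gave 51%. Enlarging the family while switching method would use up the gain.

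**The case against.** Bonferroni is valid, and choosing it contradicts nothing in the article. The rule is also conditional and secondary to the MANCOVA, and the dyadic data go to the Actor-Partner model; neither the planned 2 × 3 MANCOVA nor that model was simulated. All of this stands, and it makes the point an improvement in efficiency. It does not remove the point, because the article states the rule explicitly and Holm loses power in no scenario on the same family.

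A reader might infer that the plan forfeits a fixed 8 to 12 points on every claim. The documents do not support that. They give no family size, correlations or share of true effects. Even the eight outcomes are one reading of Table 1: section 2.4 also lists a breath counting task and two emotion-regulation scales. The 8 to 12 points are an average over true effects in the favourable case. In addition, d = 0.5 on SR outcomes is a size the plan wants to detect; section 2.1 ties its moderate effect to the SP comparison.

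A reader might also argue for Holm from the chance that all six H3.1 tests succeed, which in the t-test simulations rose from 9–12% to 32–37%. This does not favour Holm specifically. If a hypothesis counts as confirmed only when every component is significant, each component can be tested at 0.05 without adjustment.

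**Conclusion.** The point holds as a free or cheap improvement, and the stated rule is not an error. The qualitative statement, same family-wise control under any dependence and never fewer rejections, needs no assumption about this trial. The roughly 8 to 12 points require d = 0.5 on nearly every outcome, 64 evaluable per arm, and about three or more tests. Outside that case the benefit is small, down to nothing with one real effect, but it is never negative on the same family. Since the favourable case is the one the study's hypotheses predict, the change is worth making.

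**What to change.** In section 3, keep the family as now defined, the tests on the same set of dependent variables. Replace the division of alpha by the number of tests with Holm-adjusted p-values at a family-wise 0.05, for example `p.adjust(p, method = 'holm')` in R, which the article already names as its software. Do not redefine the family as all tests under a hypothesis: that could pool the visits and the within-group tests and cancel the gain.

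The cost is one sentence and one line of code. The downside is that simultaneous confidence intervals matching Holm are less simple; unadjusted or Bonferroni intervals can still be reported if labelled as such.

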## 4. Limitations

Despite the importance and innovative aspect of the study, many limitations are to be noted. First, the study is to be conducted with a Canadian English-speaking sample, which might limit the generalizability of the results to non-English speaking or non-Canadian/Western population. Repeating the study in different populations with different language, geographic and ethnic background will be highly warranted. Second, we intend to implement a brief (low dose) MBSR program, which, even has been shown to produce similar effects than the original program, might limit the effects on some specific outcomes related to interpersonal mindfulness. Third, even though mindfulness is measured with both a subjective (self-report) and objective (behavioral) measure, the use of MAAS limits the measure of mindfulness to a single dimension. Finally, mindfulness practice is only measured through self-report daily logs, which might not be accurate as participants tend to forget and might have difficulty to be objective in evaluating their own practice. In sum, most of these limitations should be addressed in future studies testing the proposed model of interpersonal mindfulness.

## 5. Significance and implications

Many studies have shown the positive effects of mindfulness training on those who engage in it, and others have shown a positive impact on interpersonal relationships, or on participants’ partners. This is the first attempt to investigate these three processes in a single study. In addition, this is the first study that grounds the study of interpersonal mindfulness in the quality of interpersonal interactions, using objective and subjective measures. Moreover, this is the first study that examines interpersonal mindfulness among unrelated (i.e., stranger) dyads. The field of interpersonal mindfulness is growing fast, however, processes of interpersonal mindfulness, that is, the mechanisms through which the positive effects of mindfulness are transferred from individuals receiving the training to those interacting with them remain unknown. Therefore, investigating the interpersonal effects of mindfulness training through the proposed model allows us to establish the theoretical and empirical basis of interpersonal mindfulness, which is crucial for future research. More specifically, this project establishes the scientific bases of the transfer of mindfulness benefits from individuals receiving mindfulness training to individuals interacting with them. In addition, the project allows to measure the effects of mindfulness meditation on prosocial processes (such as empathy, active listening, compassion toward others, quality of social emotional support) and to delineate the role of these prosocial processes in interpersonal mindfulness.

The study implements a shortened version of MBSR and MBSR is the most used MBP worldwide, increasing therefore, the external validity of the study. In addition, the longitudinal aspect of the study allows testing the long-term effects of mindfulness training on interpersonal interactions. Furthermore, the study of the effects of MBSR training on interpersonal interactions through behavior observation will reveal for which verbal and non-verbal interpersonal behaviors MBSR is effective. On the social level, delineating the active ingredients of interpersonal mindfulness and specifically the role of prosocial behaviors will allow devising and validating new and more effective interpersonal mindfulness-meditation programs, with applications in multiple fields, including parenting, teaching, counseling, physical/mental health, management, and intimate/conjugal relationships among others.

## Data availability statement

The original contributions presented in this study are included in the article/supplementary material, further inquiries can be directed to the corresponding author.
